#### Self-Administered Questionnaire

After consent and on entry to the main study, all patients but not carers will be asked to complete a self-administered questionnaire (to be developed with advice from the Patient Public Involvement [PPI] team members) with open and closed questions regarding self-awareness/perception of burden of disease, self-management including use of medication, identifying signs and symptoms of deterioration, problem-solving, seeking support/health care professional input during usual care as well as rationale and expectation of participation in the study and perceived barriers and enablers to successful completion in the study. We anticipate that this short self-administered questionnaire will take approximately 30 minutes to complete. The purpose of this self-administered questionnaire is to use individual responses to act as an “aide memoire” at the follow-up interviews.

#### Analysis

Data analysis will use the framework approach which provides a systematic, auditable, and rigorous analysis of qualitative data [10]. It is also more deductive than other thematic analysis approaches and ensures that focused data are collected to answer the clear research objectives of the study. Experienced facilitators will independently code all data. Scrutiny of the framework matrix will be sought to see if there is agreement with the categories generated. In addition, a member of the steering group not involved in data collection will be asked to independently read through a sample of the transcripts to generate a preliminary framework without seeing the original researchers’ list. In the case of disagreement, a solution will be sought to clarify the meaning of a code/theme developed until mutual consent is reached. The aim of this stage is to enhance the validity of the development of the conceptual framework and to guard against researcher bias. A narrative summary will be developed from the findings which includes comparison within case and across patient and carer’s perception and experience.

#### Discontinuation or Withdrawal of Participants From Study

Participants not complying with study requirements or failing to upload data or collect a sample will be retrained. Significant nonadherence (eg, noncollection of data and samples for a period of several weeks) may lead to withdrawal of the participant from the study by the study team. If participants and carers are not willing to continue data collection, they may decide to withdraw from the study and will be requested to return all the equipment.

#### Definition of End of Study

The end of study is the date of the last sample and data upload of the last participant follow-up date or the last qualitative interview, whichever comes last.

### Assessment of Safety

This is a noninterventional study and is therefore considered to be of no additional safety risk compared with usual clinical practice. All patients are expected to have a number of comorbidities and on-going symptoms due to their illness. All study procedures in use are the usual standard of care for this population and are not novel. The test used to observe the variation in levels of Exotoxin A is a new test but one that is validated and in itself provides no risk of harm to the participants; it is not performed on the participants themselves but on their sputum, which they would ordinarily be producing daily, and it will not change any clinical treatment as the results will not be available to the participant or their clinical team.

There is therefore no clear rationale for additional safety monitoring during the study period or for the expedited reporting of any serious adverse events. However, as study procedures are being conducted more frequently by the patients in their homes (as part of their daily routine), there may be an increased frequency of expected side effects or adverse events for some patients. The most likely adverse event during procedures is an increased risk of fainting for those participants who are susceptible to fainting during spirometry (specifically daily peak flow, which requires blowing rapidly and forcefully into a spirometer). Therefore, the following risk-adapted safety monitoring procedures are to be followed during the study period.

Participants will be asked to report any of the expected adverse events (dizziness or light-headedness and fainting) to the research team if they occur at a level which causes significant discomfort to the participant so that the research team can provide any further training or adjustments to the way in which the measurements are taken or reduce the frequency at which the participant is to take the measurement.

The chief investigator and study team will record and monitor any adverse events caused due to the increased frequency of the self-monitoring assessments. If there is any concern over these events or if they become unacceptable and in any circumstance cause the risk-to-benefit ratio to tip, they should be expedited to the sponsor and may be subsequently reviewed by the Research Quality Committee.

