Following training, questions about use of the equipment will be answered by the research nurse and referred to the company in the event of technical difficulties with the IT system. The iPads will be supplied preconfigured with all software installed and an account for the volunteer already created and defined. A remote access technical support solution will also be preinstalled allowing the company to remotely access the iPad to resolve problems in the event of significant failures. If required, follow-up visits to the participants will be undertaken. Every effort will be made to ensure that the volunteer is adequately trained and supported for the duration of the study.

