#### Clinic Visits

Participants will be required to attend the clinic for a follow-up visit at months 3 and 6 (study completion) ± 2 weeks. Participants will attend their normal review with the medical team that usually involves lung function, sputum sample for culture, and clinical review. They will then have a research visit which will involve disease-specific control and quality of life questionnaires (Quality of Life–Bronchiectasis, Short Form Health Survey, St. George's Respiratory Questionnaire, EuroQol 5-Dimension Questionnaire) as well as noting any changes to treatment and exacerbations. The data collected from these visits will be recorded on paper CRFs which will then be uploaded by a member of the research team to a local study database with restricted access.

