#### Health Economics

In preparation for a future cost-effectiveness trial of the self-management system, a questionnaire to collect health care use data will be piloted to capture resource use. These data will be analyzed descriptively. The daily questionnaire within the Activ8rlives app asks if participants have been in contact with a health professional or been in hospital in the last 24 hours. If they answer yes, they will be prompted to give more information about who they saw and for what reason. This will capture data on the participants’ health care use for their respiratory condition as well as other conditions.

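### Participants are asked to report fainting under the same discomfort threshold as dizziness, so a brief faint that did not much trouble the participant falls outside the instruction

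*Protocol article*

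**What the plan says.** All the wording at issue is in Assessment of Safety in the protocol article. The section treats the study as noninterventional and sees no clear case for additional safety monitoring or expedited reporting. It then makes an exception, because the procedures are done at home more often than usual. It identifies the main hazard: "The most likely adverse event during procedures is an increased risk of fainting for those participants who are susceptible to fainting during spirometry", pointing in particular to the daily peak flow measurement. For that reason it sets out risk-adapted procedures.

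The first of these is the instruction to participants, who are to report the expected events ("dizziness or light-headedness and fainting) to the research team if they occur at a level which causes significant discomfort to the participant". The purpose given is that the team can retrain the participant, adjust the technique, or "reduce the frequency at which the participant is to take the measurement".

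The second is a duty on the team: "The chief investigator and study team will record and monitor any adverse events caused due to the increased frequency of the self-monitoring assessments". Events that raise concern are to be escalated to the sponsor.

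**The concern.** A discomfort threshold suits a graded symptom. Mild light-headedness after a forced blow is common sense to filter out, and the participant is the right judge of whether it was troublesome. Fainting is different. The hazard is the loss of consciousness itself, with the possible fall or injury, and how the participant feels afterwards is a poor guide to it.

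At stake is whether the protocol's own safeguards are set in motion. Retraining, a change of technique or fewer measurements would all be apt after a faint with quick recovery, but the team can offer them only if it hears of the event. Study Assessments asks for the measurements once a day for 6 months, so a susceptible participant who says nothing and carries on meets the same manoeuvre the next day. The team's record of events caused by the extra measurements could also be incomplete.

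**Working it through.** No arithmetic applies. The article gives no faint rate and no count of susceptible participants, so an expected number of missed faints cannot be calculated. The check is a reading of the text in three steps.

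**1. What the condition governs.** The sentence lists dizziness or light-headedness and fainting together in one bracket, and a single conditional clause follows the list. Grammatically it covers every item. No separate rule for fainting appears in that section or anywhere else in the article.

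**2. Whether the team's recording duty removes the threshold.** That duty ("The chief investigator and study team will record and monitor any adverse events caused due to the increased frequency of the self-monitoring assessments") carries no discomfort condition. But it is a duty to record, and gives no means of detection. For an event at home the team must first learn of it.

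**3. Whether another stated route would tell the team.**

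- *Daily app questionnaire* (Participant and Carer Training; also the Abstract). It covers symptoms, medications and health care use. The symptom items are not listed, so a faint item can be neither confirmed nor ruled out. Under Data Management, clinical staff cannot see these data. The research nurse can, but for technical support and tracking progress.
- *Daily health care question* (Health Economics). It "asks if participants have been in contact with a health professional or been in hospital in the last 24 hours", so it picks up a faint only if care was sought.
- *Telephone call by the nurse* (Study Assessments). The nurse calls to ask about difficulties when data have not been uploaded. A faint that interrupts the day's readings could prompt a call; a participant who faints and still uploads everything would not get one.
- *Equipment support* (Participant and Carer Training). Here "questions about use of the equipment will be answered by the research nurse". This depends on the participant raising the matter.
- *Visits at months 3 and 6* (Clinic Visits). The research visit includes questionnaires "as well as noting any changes to treatment and exacerbations". The usual clinical review takes place on the same occasions. Neither is stated to ask about faints.
- *Monthly sample transfer* (Sample Production and Home Storage for Sputum and Urine Samples). It is described only as a matter of logistics.
- *Carers* (Exclusion Criteria, closing paragraph). They help with measurements and uploads, and are not asked to report events.

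Several of these could catch a faint. None is stated to ask about one, and none requires every faint to be reported. The thresholded instruction is the only stated request to participants to report one.

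**The case against.** The strongest reply is that this is loose drafting. The phrase about a level of discomfort plainly has dizziness in mind. The section exists because of fainting, and its evident intent is that faints are reported. The gap opens only if someone loses consciousness during a study measurement and does not regard that as significantly uncomfortable; many people would mention it anyway. The text does not say that faints should be withheld, and a reader who infers that the protocol discourages reporting them, or that faints went unrecorded, goes beyond it.

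It is also fair to say that a journal article condenses the full protocol. The app's symptom items, the case report forms for the visits and the training material are not shown and may already ask about faints. Their absence from the article is no fault, and it would be wrong to infer that no route could catch a faint. The nurse's call after a missed upload and the daily symptom questionnaire are real opportunities. The study is small, with 30 participants, and the article describes its procedures as usual care.

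Finally, recruitment is complete and the study is in data analysis, so new wording cannot reach these participants.

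Most of this stands, and it limits the size of the point. It does not remove it. The threshold is written into the article and applied to fainting by name, so the point does not rest on missing detail. Good intent does not change what the sentence asks participants to do.

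**Conclusion.** The point holds in a limited form. The participant instruction applies a discomfort threshold to the very event the risk-adapted monitoring was written to manage. A brief, quickly recovered faint that the participant does not find significantly uncomfortable falls outside it. The team's wider recording duty does not close the gap, because it depends on the team being told.

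The magnitude is low and cannot be quantified. The conclusion assumes that participants follow the instruction as worded and that the undisplayed app items and visit forms do not ask about faints; if they do, the practical gap is smaller, though the sentence still fits fainting badly. No endpoint, sample size or inference is affected. A stronger reading, that the study was unsafe or that its adverse-event record is unreliable, is not supported: nothing in the article shows that any faint occurred or was missed. What can be said is that the record may be incomplete for faints below the threshold.

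**What to change.** Split the reporting sentence in Assessment of Safety in two, along these lines: participants will be asked to tell the research team about any faint during or just after a measurement, whether or not it was uncomfortable, and about dizziness or light-headedness that causes significant discomfort. The team's responses stay as they are. As an optional backstop, add one line on faints to the month 3 and 6 case report forms, or one yes/no item to the app, if neither already has it.

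Since this study is in data analysis, the change applies wherever the wording is reused, notably in the large-scale randomised trial foreseen under Rationale for Study and Potential Impact. For the present study, any report of adverse events should state that participants were asked to report faints subject to a discomfort threshold.

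The cost is one clause, plus one form line or app item if the backstop is used, and a few more minor events to log.

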### Data Handling and Record Keeping

#### Data Collection Forms

The anonymous daily data generated by participants using the technology provided to them will be uploaded directly to the Web servers of Aseptika via 3G built into the iPad tablets provided to the participants. The anonymized data collected at the hospital visits at baseline, 3, and 6 months will be recorded on study-specific CRFs. The data recorded on these forms will then be uploaded by a member of the research team onto the local study database held at Portsmouth Hospitals Trust. This database will be password protected and kept on a secure NHS server with restricted access on a computer with restricted access in a locked room.

#### Data Management

Each volunteer will be given an account within Activ8rlives online system. Their name, NHS number, address, or any other identifying information will not be entered. Anonymity will be assured by giving each participant a unique study ID which will not be traceable to the participant. The unique study ID will be formed from 2 letters and 2 numbers (eg, SE01 for the first participant recruited into the study, SE02 for the second participant recruited).

Aseptika’s servers are located in the United Kingdom and have appropriate security measures. Access to these data will be restricted to Director-level personnel within Aseptika and to the research nurse for the purposes of technical support and to track progress of the study. Patients and carers, clinical staff, and laboratory staff will have no access to these data.

Data generated from sputum and urine analysis will be output to Excel (Microsoft Corp) spreadsheets and will be imported into the account for each volunteer to be correlated with other telemetry data. Other clinically relevant information (start of antimicrobial therapy, admission or other treatment) which is associated with an endpoint will be entered into the Activ8rlives system.

### Data Analysis

#### Description of Analysis Populations

The study is a nonrandomised cohort of a single group of patients. All subjects recruited into the study will be included in the data analysis.

#### Analysis of Endpoints

The first stage of the data analysis is to use data on the collected parameters (eg, peak flow, pulse rate, oxygen saturation, activity data) to predict when an exacerbation is likely. Control charts will be used to determine the boundaries of normal behavior for each parameter. Separate control charts will be used for each participant, as what constitutes normal behavior will vary from participant to participant. When a parameter strays from normal behavior (eg, exceeds 99% control limits), an exacerbation will be predicted.

To examine the association between predicted exacerbation and actual exacerbation, participant follow-up will be divided into periods of time (eg, 7-10 days). A comparison of actual exacerbation when exacerbation has and has not been predicted will be made. To allow for the repeat measurements over time from the same participants, the analysis will be performed using multilevel logistic regression. Additionally, the sensitivity and positive predictive value of the predictions will also be calculated. Estimated values will be presented along with corresponding confidence intervals. Further exploratory analysis using novel computing methods will be conducted.

Health care use data will be presented descriptively (eg, the frequency and type of health care contacts over the study period for different participant groups).

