### Sampling and Sample Size

Using the sputum biomarkers to predict exacerbations, we based the sample size on the difference in exacerbation frequency in time periods when an exacerbation was predicted compared to time periods when no exacerbation was predicted. This will give an odds ratio of exacerbation following detection of sputum biomarkers.

Time periods will consist of approximately 10 days, of which it will be estimated that there may be on average 12 per participant (assuming an average of 4 months of follow-up). It is estimated that an exacerbation will occur in 60% of time periods in which it is predicted and 10% of time periods in which it is not predicted. It is also assumed that a predicted exacerbation will be made in only 1 in 12 time points (8% of all time points). Using a 5% significance level and 90% power, it is calculated a total of 120 time periods will be required.

However, as there are multiple time periods from the same participant, the data values are unlikely to be independent of each other and thus the sample size requires inflating. Assuming intraclass correlation of 0.18, a design effect of approximately 3 is calculated. This implies that 360 time periods are required for the analysis. This equates to a total of 30 participants for the study. The proposed 30 participants will consist of 20 participants with chronic *P aeruginosa* infection (10 with primarily COPD and 10 with NCFB) and 10 participants with *H influenzae* infection.

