## Discussion

The SENSOR study will provide a prospective evaluation of the efficacy of this home self-monitoring system in people with chronic airway infection. The data collected will allow us to determine the key elements of the self-monitoring system for prediction of exacerbations in order to reduce the burden on monitoring on patients in future.

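### The sample size rests on a sputum-biomarker flag, but the analysis, read naturally, tests an any-parameter flag, so the two sections need to be reconciled

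*Protocol article*

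**What the plan says.** **Sizing (Protocol article, Sampling and Sample Size).** The predictor is explicit: "Using the sputum biomarkers to predict exacerbations, we based the sample size on the difference in exacerbation frequency" between predicted and non-predicted periods. The section goes on: "This will give an odds ratio of exacerbation following detection of sputum biomarkers". The planning values are these: first, "an exacerbation will occur in 60% of time periods in which it is predicted and 10% of time periods in which it is not predicted"; second, "a predicted exacerbation will be made in only 1 in 12 time points (8% of all time points"). From these, "Using a 5% significance level and 90% power, it is calculated a total of 120 time periods will be required". A design effect of about 3 raises this to 360 periods, or 30 participants.

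**Analysis (Protocol article, Analysis of Endpoints).** The first stage is to "use data on the collected parameters (eg, peak flow, pulse rate, oxygen saturation, activity data) to predict when an exacerbation is likely". Each participant has a control chart for each parameter. The rule is: "When a parameter strays from normal behavior (eg, exceeds 99% control limits), an exacerbation will be predicted". Periods with and without a prediction are then compared by multilevel logistic regression, and sensitivity and positive predictive value are added. The four example parameters are all telemetry. No biomarker-specific comparison, and no rule for combining parameters, is stated.

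**Aims.** The Primary Objective uses biomarker, telemetry and symptom data together. The Discussion says that the data will "allow us to determine the key elements of the self-monitoring system for prediction of exacerbations", so that the monitoring burden can later be reduced.

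**The concern.** The two sections attach the word predicted to different things. In the sizing it means that the sputum biomarker signalled. In the analysis it appears to mean that some collected parameter signalled.

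Two things are at stake:

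- **Attribution.** One pooled flag gives one odds ratio, one sensitivity and one positive predictive value. A positive result driven by telemetry could be read as support for the *P aeruginosa* biomarker, or the reverse. The question of which elements matter would stay open.
- **Power.** The 8% flag rate and the 60% versus 10% contrast were set for the biomarker. A flag raised by any of several parameters fires more often, and each uninformative parameter in it dilutes the contrast.

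**Working it through.** **1. The plan's own figure.** Inputs from Sampling and Sample Size: p1 = 0.60, p2 = 0.10, one flagged period to 11 unflagged (k = 11), 5% significance, 90% power. The formula is not stated. A two-sided test with continuity correction reproduces the result.

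- Pooled rate = (0.60 + 11 × 0.10)/12 = 0.1417.
- Uncorrected flagged periods: n = [1.960 × √(0.1417 × 0.8583 × (1 + 1/11)) + 1.282 × √(0.24 + 0.09/11)]² / 0.5² = 7.31.
- Corrected: (7.31/4) × [1 + √(1 + 2(1 + 1/11)/(7.31 × 0.5))]² = 9.37, rounded up to 10.
- Total = 10 × 12 = 120.
- Design effect = 1 + (12 − 1) × 0.18 = 2.98, about 3. Then 120 × 3 = 360, and 360/12 = 30 participants.
- Planned odds ratio = (0.6/0.4)/(0.1/0.9) = 13.5.

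The arithmetic is sound for one predictor that flags about 8% of periods.

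**2. Chance flags under an any-parameter rule.** Assumptions: one reading per parameter per day, all readings independent, and a 1% false-signal rate at the 99% limits. The chance of at least one signal in D days with m parameters and no real change is 1 − 0.99^(mD).

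| Parameters | 10-day period | 7-day period |
|---|---|---|
| 1 | 9.6% | 6.8% |
| 3 | 26% | 19% |
| 8 | 55% | 43% |

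Eight is a plausible count: Study Assessments lists seven daily uploads (peak flow, FEV1, pulse rate, oxygen saturation, blood pressure, temperature, physical activity), and one sputum biomarker makes eight. Only the single-parameter row is near the 8% assumed.

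**3. Dilution.** Suppose the biomarker flag performs exactly as planned, and m uninformative parameters share the flag over 10-day periods. Let f = 1 − 0.99^(10m).

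- Share flagged = 1/12 + (11/12)f.
- Exacerbation rate when flagged = [0.60/12 + 0.10 × (11/12)f] / share flagged. When unflagged it stays at 0.10.
- Power uses 360/2.98 = 120.8 effective periods and the normal approximation without continuity correction. This is why the first row exceeds 90%.

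| m | Share flagged | Rate when flagged | Odds ratio | Power |
|---|---|---|---|---|
| 0 | 8.3% | 60% | 13.5 | 96.0% |
| 1 | 17.1% | 34.4% | 4.7 | 76.5% |
| 3 | 32.2% | 22.9% | 2.7 | 48.1% |
| 7 | 54.6% | 17.6% | 1.9 | 21.6% |

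**4. Attribution.** Let one source perform as planned and a second be pure noise, flagging 1 in 12 periods independently.

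- Share flagged = 1/12 + (11/12)(1/12) = 0.160.
- Rate when flagged = (0.0833 × 0.60 + 0.0764 × 0.10)/0.160 = 0.361.
- Odds ratio = (0.361/0.639)/(0.1/0.9) = 5.1.

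The result is the same whichever source is the informative one. This shows what pooling does; it is not evidence that the plan pools.

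**The case against.** The strongest reply is that pooling is an inference. Charts are kept for each parameter, and the rule speaks of a parameter, so the text also allows one series of predictions per parameter, each compared with actual exacerbations. Step 2 lends this some support, because the sizing fits a single-parameter flag. The list of parameters is only illustrative and also omits FEV1, weight, temperature and blood pressure, so the biomarker's absence from it does not exclude the biomarker. Data Management imports the sputum results to be correlated with telemetry, a secondary objective relates biomarkers and telemetry to outcomes during and after treatment, and further exploratory analysis is planned. The article is condensed, and model terms and combination rules are commonly left to an analysis plan.

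Much of this stands. A reader might infer that the study cannot show whether the biomarker, or anything else, predicts exacerbations. The documents do not support that: a pooled flag would still test the system as a whole, and the daily data would support models by element. A reader might also think that the study is named for the biomarker. Its name refers to self-management checks and *P aeruginosa* exacerbations, and its primary objective includes telemetry and symptoms.

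What the reply does not remove is the mismatch between two stated sections. On the per-parameter reading, the analysis section still does not say which prediction the sample size belongs to. The correlation work is not exacerbation prediction, and the exploratory methods are unspecified.

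**Conclusion.** The point holds as a conflict to be reconciled. The sizing section promises a biomarker odds ratio, and the analysis section states no comparison that would deliver it. On its natural reading, the analysis gives a pooled odds ratio that cannot be credited to the biomarker or to any single element, although it can show whether the whole system predicts.

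The pooled flag also fails to match the sizing: chance alone would flag roughly 26% to 55% of 10-day periods with three to eight parameters, against 8% assumed. These figures rest on independent daily readings and a 1% false-signal rate. Correlation between parameters or days would lower them, and informative parameters would soften the dilution in step 3. The odds ratios and powers there are therefore illustrations of direction, not estimates of the study's actual power.

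**What to change.** In Analysis of Endpoints:

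- Define the prediction flag separately for the sputum biomarker(s), telemetry and symptoms, and state the rule for the combined flag.
- Name the biomarker-flag odds ratio as the estimate to which Sampling and Sample Size refers.
- With the same multilevel logistic model, report the odds ratio for each flag alone and for the combined flag, which serves the primary objective. Report sensitivity and positive predictive value for the same flags.

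If the combined flag is kept as the main analysis, restate in Sampling and Sample Size the flag rate and power that apply to it.

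The cost is some wording and a few more model terms on data already collected. The intervals for the individual terms will be wider than for one pooled flag. Because the article reports that the study is already in data analysis, the change should be documented under its own provision for deviations.
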